#### Feasibility of DHTS and motor complications diary

To assess whether the DHTS and motor complications diary are feasible for everyday use in PwP, this study will assess their feasibility (see data analysis section for details).

### Patient and public involvement

As this study is a substudy of the ‘Mobilise-D—Clinical Validation Study’ insights from patient and public advisory groups which informed the Mobilise-D study were used to inform the development of this study. The Mobilise-D Study PIS was reviewed and modified by relevant patient groups and was used as a guide for this study’s PIS. Participants in this study will provide feedback on usability of the DHTS, which will inform future studies. Study insights will be fed back to patient stakeholder groups within the Mobilise-D consortium.

### Data and statistical analysis

#### Data analysis

To quantify DMOs, mobility data from the IMUs will be analysed using validated Matlab algorithms (R2019a, Mathworks, California, USA).^37 39^ To investigate the effect of medication on DMOs, medication intake timestamps (captured via the smartwatch) and mobility data from the IMU will be used. The effect of contextual factors (eg, weather conditions and probability of being indoors/outdoors) on DMOs will be considered when interpreting the medication and mobility data.

Responses to open-text questions will be analysed using a hybrid approach, with both deductive and inductive methods used to analyse responses. Responses will be grouped into three themes: feasibility, usability and recommendations for improvement. Once grouped, key subthemes within each group (ie, ease of use for the usability theme) will be identified following the same approach.

To assess the feasibility of the DHTS devices and the motor complications diary, we will assess whether the intended data was collected; specifically contextual data, self-reported medication adherence data, and mobility data for the smartphone, smartwatch, and IMU, respectively; and motor complications data for the motor complications diary.^40^ A summary of feasibility measures and their outcomes is included in table 2.

**Table 2 T2:** Summary of feasibility and outcomes extracted from DHTS and motor complications diary

Device	Measure of feasibility	Outcomes extracted
Smartphone	Percentage of datasets collected over 7 days and percentage of days missing	Number of steps taken outside the participant’s home, per day
Smartwatch	Percentage of participants interacting with the smartwatch over 7-day monitoring period	No of interactions recorded on smartwatch
Inertial Measurement Unit	Percentage of datasets collected over 7-day monitoring period	Walking speed and number of steps per day
Motor complications diary	Percentage of diaries returned and legible	Time spent in an ON/OFF state or experiencing dyskinesia

DHTS, digital health technology system; IMU, inertial measurement unit.

Only participants whose mobility data are collected for at least 3 days will be included in analysis. If participants do not complete one of the study assessments (eg, Short Physical Performance Battery) or their data from the devices is not collected, their remaining data will still be included in analysis. Assuming missing data is at random, modern statistical techniques will be used to handle missing data and will be compared with a complete case approach.^41^

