### Diary to monitor motor complications

During the 7-day monitoring period, participants will fill in a motor complications diary (paper based) for each day, indicating their ‘OFF-status’ (when they feel their medication is not working) and whether they experienced dyskinesia (involuntary movements). The diary will record data over 16 hours each day from 6:00 to 22:00 hours, from days 1 to 7 (online supplemental material 4).

10.1136/bmjopen-2023-073388.supp4Supplementary data

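### Table 2's smartwatch and diary feasibility percentages do not measure how much of the planned data was obtained, so they can overstate data yield

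*Protocol article*

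**What the plan says.** The section on feasibility of the DHTS and the diary gives the purpose: "To assess whether the DHTS and motor complications diary are feasible for everyday use in PwP". The Data analysis section makes this operational: "we will assess whether the intended data was collected". It names the data meant for each tool: adherence data for the smartwatch and motor complications data for the diary.

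Table 2 then fixes the measures:

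- **Smartwatch.** Feasibility measure: "Percentage of participants interacting with the smartwatch over 7-day monitoring period". Outcome extracted: "No of interactions recorded on smartwatch".
- **Diary.** Feasibility measure: "Percentage of diaries returned and legible". Outcome extracted: "Time spent in an ON/OFF state or experiencing dyskinesia".
- **Smartphone, for comparison.** Feasibility measure: "Percentage of datasets collected over 7 days and percentage of days missing".

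The diary's recording window is set in its own section: "The diary will record data over 16 hours each day from 6:00 to 22:00 hours, from days 1 to 7". The smartwatch section describes reminders at each Parkinson's medication time, answered yes or no, and a separate option to log as-needed medication. It gives no number of prompts per day. No target or cut-off for feasibility appears for any device.

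**The concern.** The two measures do not match the definition they are meant to serve. The watch measure takes the participant over the whole week as its unit and does not relate responses to prompts. The diary measure asks that the booklet comes back and can be read, not that it has been filled in. Both can be close to 100% when little of the planned data exists.

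These data matter beyond the feasibility report. Watch-captured adherence is one of the two primary outcomes in the section on the seven-day remote monitoring period. The watch's intake times are the reference points for the medication-effect analysis. The diary is to be used to tune the time series models. The only minimum-data rule in the article, at least 3 days, concerns mobility data and does not cover the watch or the diary. For adherence, an unanswered prompt is also different from a prompt answered no, and a percentage of participants cannot show how many prompts went unanswered.

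**Working it through.** There is no feasibility figure, target or threshold in the article to reproduce. The check therefore compares what each Table 2 measure would record with the share of planned data obtained.

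**Inputs**

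- Monitoring period: 7 days (article).
- Participants: 55 (article).
- Diary window: 16 h a day for 7 days, so 16 × 7 = 112 h (article).
- Prompts per day: not given. Assumed to range from 2 to 8.

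**Smartwatch.** Scheduled prompts = 7 × prompts per day. Completeness = prompts answered / scheduled prompts.

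| Prompts/day (assumed) | Scheduled in 7 days | One response in the week | One response a day |
|---|---|---|---|
| 2 | 14 | 1/14 = 7.1% | 7/14 = 50% |
| 4 | 28 | 1/28 = 3.6% | 7/28 = 25% |
| 8 | 56 | 1/56 = 1.8% | 7/56 = 12.5% |

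On the literal wording, every participant in this table is counted in full. If all 55 responded once, Table 2 would show 55/55 = 100%, with 1.8% to 7.1% of prompts answered.

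**Does the interaction count in the same row help?** It has no expected number to be set against. At 3 prompts a day, full response is 3 × 7 = 21 interactions. At 8 a day, 21 interactions is 21/56 = 37.5%. The same count can therefore mean complete or poor response. Unless as-needed logs are separated, they may also be mixed into the count.

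**Diary.** Completeness = hours filled / 112.

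- One of seven days filled: 16/112 = 14.3%.
- One hour filled: 1/112 = 0.9%.

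If legible, either diary counts in full. Fifty-five returned diaries with one day filled would show 100% at 14.3% completeness. This illustration takes unfilled entries as missing, which depends on the form (see the objection).

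**Comparison across rows.** The smartphone row reports missing days alongside datasets collected. The watch and diary rows have no counterpart.

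**The case against.** The strongest reply has five parts.

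1. **No decision rule.** A reader might infer that a barely used watch or a mostly blank diary would be declared feasible. The article does not support that. It gives descriptive percentages without a cut-off, so such cases enter the numerator but pass no test. This stands and limits the point.
2. **Feasibility is not a listed objective.** The five numbered objectives in the Introduction do not include it. It is a declared assessment in the abstract and in its own section. This stands, and the point should not be argued as if a main objective failed.
3. **Low use would still show.** Interaction counts and diary time are extracted and summarised descriptively, and open-text answers are grouped under a feasibility theme. This holds in part: very sparse use would probably be noticed. But neither outcome is related to an expected amount, and nothing links them to the feasibility percentage.
4. **The article is a condensed summary.** What counts as interacting could be defined in the full protocol. That may be so for a minimum number of responses. But Table 2 states the unit (participants, over the week) and the diary condition (return and legibility), and neither measures yield as the preceding text defines it. The IMU row, which counts datasets without saying what a dataset needs, is just as open. The internal contrast therefore rests on the smartphone row alone.
5. **A blank diary hour may not be missing.** The diary section has participants indicate OFF status and dyskinesia, and the form itself is not shown. If only those states are marked, an unmarked hour may mean ON. This stands, and it makes any hour-level diary measure conditional on the form.

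The extreme cases in the working are illustrations, not forecasts. The article gives no data on actual use.

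**Conclusion.** The point holds as a mismatch between a stated purpose and two stated measures. Feasibility is defined by the data obtained, yet the watch and diary percentages are insensitive to how much was obtained. On the literal wording, a fully counted participant may have answered as little as 1.8% to 7.1% of prompts (assuming 8 to 2 a day). A fully counted diary may be 14.3% complete with one day filled, provided that unfilled days are missing. The consequence is a reported percentage that can overstate data yield. It is not a formal wrong decision, because no threshold exists, and it does not by itself bias the primary analyses. The change is worth making because it is cheap and the watch data carry a primary outcome.

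**What to change.** **Smartwatch.** Make the feasibility measure the percentage of scheduled prompts answered, yes or no, per participant, summarised as median and IQR. Add the number of days with at least one response. Count as-needed logs separately.

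**Diary.** Add the percentage of the 7 diary days completed, with unreturned diaries as 0%. Use the percentage of the 112 hours instead only if the form distinguishes ON from unfilled. State in advance what makes a day completed, since a day without marks could be a day without OFF time if the form records only OFF and dyskinesia.

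**Both.** Keep the present percentages as descriptive extras.

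**Cost.** No new participant procedure is needed. Reminder times are entered by a researcher, and the third objective in the Introduction lists reminders, logged intake times and acknowledged intakes among the data recorded. The article does not say that each delivered or unanswered prompt is logged. If it is not, the entered schedule can supply the denominator. Paper diaries need manual counting, including those of the 30 participants already completed. There is a little extra analysis, and the feasibility figures may look less favourable than under the present wording.

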### Statistical analysis

Participants’ descriptive, clinical and Parkinson’s specific characteristics, as well as data derived from the DHTS and motor complications diary data, will be analysed using descriptive statistics, including percentage and frequency, mean and SD or median and IQR, as appropriate.

Functional data analysis and deep learning techniques^42^ will be used to model and predict DMO response to medication, and potential effects of contextual factors. DMO trends will be analysed between medication intake times and wearing-off effects will be evaluated via a customised scoring system. This scoring system will identify the wear off periods, grouping them relative to the strength of their effect. Non-linear time series analysis will assess changes in DMOs between medication intakes.^39 43^ Data collected using motor complications diaries will be used to optimise time series modelling of DMOs.

Should the data collected require an adjusted methodology, proposed statistical methods will be amended following completion of data collection.

#### Data collection, storage and archiving

To maintain confidentiality, participant data will be collected in a coded, anonymised manner using unique identification codes. Data will be directly uploaded onto the e-SC CiC platform or via third-party platforms (eg, weather data). All researchers will be trained to correctly enter and upload data to relevant platforms. All data collected on paper case report forms will be signed, dated, scanned and uploaded onto a secure network drive with restricted access. The e-SC CiC platform will be implemented using secure Amazon Web Services located within the European Union. The clinical site will keep original records of all paper forms in secure conditions until the study is completed. Long-term data storage will be in accordance with the Newcastle Joint Office policy for archiving, with data security arrangements made in accordance with Newcastle upon Tyne National Health Service (NHS) Foundation Trust policies. The clinical site will be responsible for archiving study documents for a period which is in keeping with the institutional or national guidelines pertaining to the site. Detailed information on the data transfer pipeline is summarised in online supplemental material 6.

10.1136/bmjopen-2023-073388.supp6Supplementary data

## Ethics and dissemination

This single-centre study is sponsored by the Newcastle upon Tyne Hospitals NHS Foundation Trust (NuTH) UK. Ethical approval was obtained from the London—142 Westminster Research Ethics Committee (REC reference: 21/PR/0469). The study will be conducted in accordance with Good Clinical Practice standards, the Declaration of Helsinki and The European Code of Conduct for Research Integrity.^46^ This study will be included in the NIHR Clinical Network Portfolio and has been registered in the ISRCTN registry (ISRCTN number: 13156149). Informed consent will be obtained by a trained researcher. The NHS indemnity scheme and Newcastle University are liable for harm to participants arising from the management and conduct of the study, and from its design, respectively.

As this is an observational study, there is no adverse event reporting planned. Should any serious adverse events (SAEs) which are related to the administration of the research procedure occur, the sponsor and chief investigator will be informed. On behalf of the sponsor, the Newcastle Joint Research Office Governance Team will be responsible for assessing protocol deviations, serious breaches and violations, as well as reporting Serious Breaches to the REC. The chief investigator is responsible for reporting protocol deviations and violations. Any protocol amendments will be communicated to the sponsor with all required amendment documents completed. The sponsor will be required to agree and accept any modifications, before amendments can be submitted to the NHS REC for their approval.

### Dissemination policy

Newsletters will be sent to participants to inform them of study outcomes. Research will be disseminated through peer-reviewed scientific journals, internal reports, conference presentations and relevant websites. We will follow the International Committee of Medical Journal Editors recommendations for authorship eligibility.

### Access to data

We plan to indefinitely maintain the complete, anonymised dataset on the e-SC platform. On study completion, this dataset will be made available to the wider research community; on request and will be shared with approved collaborators nationally and internationally for peer review, scientifically sound studies. Participants will have the right to access a copy of their data or request its removal following an appropriate request. These rights will terminate following dataset anonymisation and after the study key code is destroyed. The lead clinical investigator has overall responsibility for study execution and can access the full dataset. Data analysts, who are responsible for implementation of data protocol, will have access to the full-anonymised dataset. Statisticians will only have access to the full-anonymised datasets and will not have access to raw data files. Access to study data will be given to authorised representatives from the sponsor, host institution and regulatory authorities to allow study related audits, monitoring and inspections—in line with participant consent.

### Study status

The first phase of recruitment has finished, with data collected in 30 PwP. Recruitment for the second phase of the study will start in February 2023 and will continue until June 2024 or until the desired sample size has been reached.
